## Abstract

**Background:**

Despite weak evidence, the use of acupuncture has increased in infantile colic. The only three randomized trials conducted evaluated standardized minimal acupuncture in one single point. Two showed effect but one did not so further research is necessary.

The aims of the study are 1) to test if results in earlier trials conducted in private acupuncture clinics can be repeated at Child Health Centers (CHC) and 2) to compare the effect of two types of acupuncture and no acupuncture in infants with colic at CHC.

**Methods/design:**

a multicenter randomized controlled three-armed trial for infantile colic conducted in four regions of Sweden. Alongside the standard program at their regular Child Health Center infants visit a study center twice a week for 2 weeks. The infants are randomly allocated into three groups.

According to the power analysis, 144 otherwise healthy infants aged 2–9 weeks old, who – according to parents’ registration in a diary – are crying and/or fussing more than three hours per day, more than 3 days per week will be included. Parents register daily in the diary during the baseline week, two intervention weeks, and one more week directly after the last study visit.

At four study visits at the Child Health Center parents meet a nurse for 20–30 min to receive advice and support. The nurse and the parents are blinded for group allocation. Infants are carried to another room, where they spend five minutes with an acupuncturist. Infants randomized to group A receive standardized minimal acupuncture in LI4. Group B receive individualized acupuncture where, according to symptoms, the acupuncturist can choose between the points Sifeng, LI4, and ST36. Group C receives no acupuncture.

The primary outcome is relative difference in crying, counted in minutes. Secondary outcomes are number of infants fulfilling the criteria for colic, and changes in sleep and stooling frequency. Adverse events and blinding are recorded.

Recruitment started in January 2013. During the first 14 months 93 patients were included. Data collection continues until May 2015. No interim analyses have been conducted.

**Discussion:**

The study will provide information about the efficacy and safety of acupuncture as a complement to usual care in infants with colic.

**Trial registration:**

December 29, 2012: ClinicalTrials.gov NCT01761331

## Background

Infantile colic, defined as crying and/or fussing for more than three hours per day, more than 3 days per week, affects 10–20 % of newborns [1] and thus is a relatively common problem. Both infants and parents suffer, and there is a risk of delayed early attachment [2, 3]. Eliminating cow’s milk protein resolves the colic in 20 % of afflicted infants. Currently, no other conventional treatment exists that is both safe and effective, and the use of complementary medicine is increasing. Acupuncture for infantile colic is used in many countries [4] despite weak evidence. The Swedish Council for Health Technology Assessment (SBU) suggests that patients may benefit from acupuncture [5], although it is rarely provided within the Swedish public health system. To this date no serious side effects have been reported.

It is plausible that acupuncture can have effect in the treatment of colic, as acupuncture releases different neurotransmitters and hormones, has both calming and analgesic effects, and affects digestion [6]. The only three published randomized controlled trials were conducted in private clinics and evaluated standardized minimal acupuncture in one single point. Two of the trials used the acupuncture points Large Intestine 4 (LI4) [7, 8] and report a small but significant reduction in crying in the acupuncture groups compared to the control groups. In one of them [8], the needle was stimulated for 20 s; in the other, for only two seconds [7]. A third RCT evaluating the effect of the acupuncture for 30 s in the acupuncture point Stomach 36 (ST36) found no significant difference between groups [9].

Traditional Chinese Medicine (TCM) is a complex and diverse form of therapy, encompassing several styles of acupuncture, among other medical practices. In clinical practice, most TCM acupuncturists differentiate between syndromes and select acupuncture points and needle techniques according to a diagnosis. Diagnoses can, for example, be based on the patient’s pulse, constitution, and signs of “heat” or “cold” [4]. There is a discussion whether the effect of acupuncture depends on the points used or not [10, 11]. TCM acupuncturists claim that point specificity and the choice of points according to patients’ symptoms and signs are vital [4]. For this reason, TCM practitioners select points at each treatment session to match each patient’s most current symptoms. This means that in clinical practice, the same point is rarely chosen for all patients with a specific condition, such as colic, and treatment is rarely given in one single point [4]. That is to say, the trials conducted so far might not reflect clinical practice. Further research is warranted, and trials evaluating clinical practice should be conducted.

In earlier trials conducted at private acupuncture clinics, minimal acupuncture in LI4 reduced the crying in infants with colic. If acupuncture to infants is to be implemented in the public health care it should be given at CHC. The aims of the study are 1) to test if results in earlier trials conducted in private acupuncture clinics can be repeated at Child Health Centers (CHC) and 2) to compare the effect of two types of acupuncture and no acupuncture in infants with colic at CHC.

## Methods

### Design

A multicenter randomized controlled trial, called ACU-COL, started in January 2013 and will collect data until May 2015. ACU-COL is performed with three parallel arms at Child Health Centers (CHC) in four regions of Sweden, and measures the effect of acupuncture in reducing symptoms in infants with colic. Two of the four study centers are located outside the second and third biggest cities in Sweden and the remaining two in smaller cities. Two types of acupuncture (standardized minimal acupuncture in LI4 and individualized acupuncture) are compared to an untreated group.

### Participants

Otherwise healthy infants not more than 8 weeks at registration and not more than 9 weeks when the intervention begins.

Inclusion criteria: infants who, according to parents’ record in the diary, cry and/or fuss more than three hours per day, more than 3 days per week were included and randomized. Infants should have tried a diet excluding cow’s milk protein for at least 5 days.

Exclusion criteria: being born before week 37, not gaining weight properly, having tried acupuncture, or taking any kind of medication (apart from dimeticone or lactobacillus reuteri).

### Participant enrollment

Information about ACU-COL was given to CHC nurses within about 80-km radius of each study center. Parents received information about the trial from nurses and physicians at their ordinary CHC or web-based information via a website (www.spädbarnskolik.se).

Parents who wanted to participate in the trial contacted the project leader (KL) for further information. The project leader checked that the infant was suitable for the trial (Form A) and instructed parents to register the infant’s fussing, crying, colicky crying, sleeping, feeding, and stooling daily in a validated diary (Form B) during a baseline week used for selection. Infants who according to the diary had cried/fussed more than three hours/day more than 3 days and thereby had fulfilled the criteria for colic were included and randomized provided that the parents signed informed consent.

### Randomization

Infants were randomly allocated into one of three groups in proportions of 1:1:1, following randomization lists performed by an independent center for clinical research and development (R&D, Region Skane). The infants were randomized in two strata: infants aged 2–5 weeks and infants aged 6–9 weeks and therefore two randomization lists were created for each of the four centers. Infants were assigned to the three different treatments by sampling without replacement from a block consisting of, to the investigator, unknown number of labels from each treatment group. Researcher and clinicians had no influence on the allocation of infants.

### Blinding

When an infant was included, the project leader informed a project coordinator, who was in charge of the randomization. The coordinator kept the randomization lists confidential and had no contact with or information about the families. The coordinator sent the study number via e-mail to the nurse at the study center and to the project leader, as well as the study number and group allocation to the acupuncturist. The acupuncturist’s records, including the group allocation, were stored in a locked briefcase that only was available for the acupuncturists. Essentially, only the coordinator and the acupuncturist knew each infant’s group allocation. None of them met the parents or discussed the infants with study nurses.

### Usual care

Parallel to the intervention, all infants followed the standard program at their regular Child Health Center (CHC), which includes a weekly visit to a nurse during the first month of life, every second week the second month, and one visit the third month. At these regular visits, the infants are weighed and measured, and the parents get childcare advice.

### Interventions

Parallel to usual care, study participants visited a study CHC where the intervention was conducted twice a week for 2 weeks. Parents met a nurse for 20–30 min. Parents described their situation, discussed the infant’s symptoms, and got evidence based support and advice. All parents received the information that having a baby with colic can be exhausting, and the nurse attempted to give them hope. The nurse informed parents about normal crying, that a healthy 6 week old infant cries an average of 1.5–2.5 h per day and that colic does not negatively affect the child’s development. Breastfeeding mothers were encouraged to continue to do so.

At each of the four study visits, the study nurse brought the infant to a separate treatment room where another nurse, trained in acupuncture, was alone with the infant for approximately five minutes. The acupuncture nurse treated the baby according to allocation and recorded treatment provided, as well as whether the baby cried and, if so, for how long. Adverse events and how they were dealt with was also recorded (Form E). After five minutes, the acupuncturist called the study nurse, who then carried the baby back to the parents.Group A:Infants received standardized minimal acupuncture in LI4. One needle was inserted approximately 3 mm deep in the point LI4 on the infant’s hand unilaterally for 2–5 s and then withdrawn.Group B:Infants received individualized acupuncture and the needles could be retained longer. A guideline for the choice of points was developed based on a previous practitioner survey conducted with experienced acupuncturists specialized in pediatrics [4]. It allowed acupuncturists to choose any combination of the acupuncture points Sifeng, LI4, and ST36, based on the symptoms reported in the diary. Maximum 5 needles were inserted approximately 3 mm. The point Sifeng was considered as four insertions, needled about one second each. Needles in LI4 and ST36 were retained for maximum 30 s each.Group C:Infants spent five minutes with the acupuncturist in the treatment room. The nurse held the infant’s hand and spoke to him/her in a calm voice.

### Sample size

ACU-COL was designed to compare the effect of two types of acupuncture and no acupuncture in infants with colic. According to the power analysis, conducted by an independent statistician at the center for clinical research and development (R&D, Region Skane) and based on the results in an earlier trial with the primary outcome crying [7], 192 infants will be needed to detect a statistically significant difference between the two acupuncture groups assuming that a clinically relevant difference in crying per day between group A and group B is 30 min which is 11 % in relative difference between the first and the second intervention week compared to the baseline week.

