#### Statistical analysis

Statistical analyzes will be made from the data collected in forms and records (see Table 1), and carried out following a structured data management plan and by using appropriate statistical methods (dependent upon type and variable) for descriptive data as well as multivariate analysis.

We will analyze usual care plus standardized minimal acupuncture (group A) and individualized acupuncture (group B) versus usual care plus four extra visits to a CHC (group C). The mean difference over time and between groups in reduction in % of colicky crying, crying and fussing in minutes/day will be compared using relevant statistical methods depending on distribution.

We will use analysis of covariance at the baseline week, the first intervention week, the second intervention week and the week after the last visit to the study center to assess whether clinical differences, if any, are significant.

How many infants in each group who still cries and/or fusses more than three hours/day more than 3 days per week, i.e. fulfills the criteria for colic, each intervention week will be assessed by the difference in survival curves (days to crying <3 h/day) using Kaplan–Meier analysis.

Additional descriptive measurements will be presented on back ground data, the acupuncturists’ choice of points for group B, results on separate study centers and on blinding.

All data in this trial will be assessed by SPSS v22.0 (SPSS, Chicago, IL, USA). P <0.05 will be considered statistically significant.

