### Trial status

Recruitment began in January 2013. During the first 14 months, 93 infants were included. Data collection will continue at least until May 2015. No interim analyses have been conducted. Analysis of data is expected to be complete during Autumn 2015, followed by submission to a peer-reviewed journal in December 2015.

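### The abstract gives 144 infants and the sample-size section 192, both credited to the power analysis, and nothing in the article reconciles them

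*Protocol article*

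**What the plan says.** The protocol article gives a planned size in two places.

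- Abstract, Methods/design: "According to the power analysis, 144 otherwise healthy infants aged 2–9 weeks old" who meet the diary criteria for colic are to be included. No contrast, effect or power is attached to this figure.
- Methods, Sample size: "192 infants will be needed to detect a statistically significant difference between the two acupuncture groups". The effect is specified as follows: the clinically relevant "difference in crying per day between group A and group B is 30 min which is 11 % in relative difference". The calculation is described as "based on the results in an earlier trial with the primary outcome crying".

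Three other sections bear on the point. Under Randomization, "Infants were randomly allocated into one of three groups in proportions of 1:1:1". Under Statistical analysis, "P <0.05 will be considered statistically significant", without saying whether tests are one- or two-sided. Trial status reports 93 infants included in 14 months and no interim analyses, but names no target.

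**The concern.** Both totals are current text and both are credited to the power analysis, yet 192 is a third more than 144. The planned size is the yardstick for judging whether the trial recruited as intended and how much weight a null A-versus-B result can bear. With two figures and no statement of how they relate, a reader cannot tell which one governs, and the power for the 30 min/day difference depends on the answer.

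**Working it through.** **Inputs from the article**

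- Totals: 144 (abstract) and 192 (Sample size).
- Allocation 1:1:1 (Randomization): 144/3 = 48 per arm and 192/3 = 64 per arm.
- Effect: 30 min/day between A and B, equated with 11%, which implies a baseline of 30/0.11 = about 273 min/day (Sample size).
- Alpha 0.05 (Statistical analysis).

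**Assumptions, because the article does not give them:** two-sided testing, a two-sample comparison of means, and power of 80% or 90%. The SD is unknown.

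**Step 1: can either total be reproduced?** No, because SD, power and dropout allowance are not stated. One can only solve backwards for the SD that each total would need. With n per arm, the standardized effect is d = (z_alpha + z_power) × sqrt(2/n), and SD = 30/d.

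| Total | Per arm | Power | d | SD needed (min/day) |
|---|---|---|---|---|
| 192 | 64 | 80% | (1.960 + 0.842) × sqrt(2/64) = 0.495 | 60.6 |
| 192 | 64 | 90% | (1.960 + 1.282) × sqrt(2/64) = 0.573 | 52.4 |
| 144 | 48 | 80% | (1.960 + 0.842) × sqrt(2/48) = 0.572 | 52.5 |
| 144 | 48 | 90% | (1.960 + 1.282) × sqrt(2/48) = 0.662 | 45.3 |

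None of these SDs can be ruled out from the article, so neither total is shown to be wrong.

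**Step 2: what does the choice cost?** Hold d at the value that 64 per arm would detect and compute power at 48 per arm as Phi(d × sqrt(48/2) − 1.960).

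- If 64 per arm gives 80%: 0.495 × 4.899 − 1.960 = 0.466, so power is about 68%.
- If 64 per arm gives 90%: 0.573 × 4.899 − 1.960 = 0.847, so power is about 80%.

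The exact t-test gives 67.7% and 80.0%, the same after rounding. The loss is about 10 to 12 percentage points.

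**Step 3: detectable difference at 48 per arm.** If 64 per arm was sized for 80% power at 30 min/day, the difference detectable with 80% power at 48 per arm is 30 × sqrt(64/48) = 34.6 min/day (34.7 by the t-test), about 35. If 64 per arm was sized for 90%, then 48 per arm still detects 30 min/day with about 80% power.

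**Step 4: could the two totals belong together?** Four unstated assumptions would each turn one into the other:

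- 80% against 90% power: (3.242/2.802)² = 1.339, and 144 × 1.339 = 193.
- 25% dropout: 144/0.75 = 192.
- Bonferroni adjustment for three comparisons at 80% power: ratio 1.334, and 144 × 1.334 = 192.
- A and B pooled against C (2:1) with the same standardized effect: (1/n + 1/(2n)) = 1.5/n replaces 2/n, so n = 0.75 × 64 = 48 in group C and 144 in all.

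The article states none of them, so none can be chosen. They also have different consequences. Under the power link, 144 is a weaker but conventional design for A versus B. Under the dropout link, 192 is the number to enrol. Under the pooled link, 144 would leave A versus B, the only contrast the Sample size section sizes, below the power of 192.

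**The case against.** The best defence is that one power analysis can yield several sample sizes. The Sample size section ties 192 to A versus B, the abstract ties 144 to no contrast, and the Statistical analysis section describes the acupuncture groups against group C. The two figures may answer different questions. This stands as far as it goes: it means neither number can be called an arithmetic error. It does not remove the inconsistency, because the article offers no such explanation and presents each figure without qualification as what the power analysis requires.

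It is also fair to say that an article may leave SD, power and dropout to the full protocol. Their absence is not the point here. Likewise, the power figures above use a t-test on minutes, whereas the outcome is a relative difference and analysis of covariance is planned, so they indicate the scale of the effect and no more.

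A reader might infer three stronger things that the article does not support:

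- **That 192 covers only the two acupuncture groups (96 per arm, 288 in all).** The sentence follows a description of the three-group design, and neither 96 nor 288 appears anywhere. The total over three arms is the natural reading.
- **That the end date proves 192.** At 93/14 = 6.64 infants per month, 144 is reached at month 21.7 and 192 at month 28.9, close to the end of May 2015. But May 2015 closes data collection, not recruitment. Each infant needs two intervention weeks and 6 further days, about 0.7 months. Counted from 1 January 2013, inclusions completing by then would be about 6.64 × 27.3 = 181 (end on 1 May) to 6.64 × 28.3 = 188 (31 May). The exact start day is not given and a constant rate is assumed. The date sits nearer 192 but does not settle the matter.
- **That the trial is free to stop when the results suit.** Trial status does say "Data collection will continue at least until May 2015", where the abstract has no such qualifier. That is a small difference in wording, and both places report that no interim analyses were done. Nothing points to outcome-driven stopping.

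**Conclusion.** The point holds as an internal inconsistency: 144 and 192 are both attributed to the power analysis for the same three-arm trial, and at least one is wrong or lacks the condition that would reconcile it with the other. Neither is shown to be miscalculated. Assuming a two-sided 5% t-test of A against B, and taking each figure as the total over three arms, 48 per arm gives about 68% power if 64 per arm gives 80%, and about 80% if 64 per arm gives 90%. Whether 144 is adequate for A versus B therefore turns on a power level that the article does not state. It should be corrected, because the planned size is what completion and a null result will be judged against.

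**What to change.** State one target in the abstract and in the Sample size section, as a total and per arm, with the contrast and power it belongs to. If both figures are meant, say which contrast, power level or dropout allowance each refers to.

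- If 192 governs, replace 144 in the abstract.
- If 144 governs, replace 192 and restate the power, or the detectable A-versus-B difference, for 48 per arm. The value of about 35 min/day applies only if 64 per arm was sized for 80% power.

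The cost is wording only. If 144 is the real target, the stated power or detectable difference may become less favourable.

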#### Outcome measurement

Primary outcome is relative difference in crying (mean values for the sum of fussing, crying and colicky crying) during the baseline week, during each of the two intervention weeks and during 6 days after the last treatment.

A secondary outcome is how many infants in each group who still cries and/or fusses more than three hours/day more than 3 days per week; i.e. fulfills the criteria for colic, each intervention week. Other secondary outcomes are change in frequency of stooling per day and change in hours of sleep per day during the same time frames. Adverse events, eventual parallel treatment or medication, how much infants cried from being needled and how well parents are blinded will be reported. Points chosen by the acupuncturists for infants in group B will be reported.

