### Data collection

Parents register in the diary (Form B) daily during the base line week, two intervention weeks, and 6 days after the last visit at the study CHC. The study nurse collects the diaries at the study visits. The diaries from the follow up week are sent to the project leader by mail.

At the first visit the nurse collects demographic data (Form C) and information about smoking, allergies, colic in the family, complications, and the mother’s intake of prescribed medication during the pregnancy and after the delivery. Information about the infants’ feeding, birth weight, when the excessive crying started, and use of probiotics, dimeticone, herbal treatment, etc. is also collected in Form C.

In Form D parents’ experiences of changes in the infants crying, stooling and sleep as well as their perception of if their infant has received acupuncture or not, and whether they have noted any side effects associated with acupuncture are reported.

The acupuncturist note in a Form E which of the points that was used, time for stimulation, possible crying and if so for how long.

One week after the fourth visit, and after the parents have sent in the diary for the last week parents are phoned and asked the questions in Form D once more. Parents also report eventual treatments or medication provided by the CHC or by other therapists parallel to the study participation (Form F). Thereafter the parents are told their infant’s study allocation.

When each of the instruments is used in the trial is described in Table 1.

**Table 1 Tab1:** Telephone contacts, visits and instruments

	Baseline week for selection of infants fulfilling the criteria for colic		Intervention week 1		Intervention week 2		Follow up	
Telephone	Form A	Form A						Form F
Parents daily registration in a diary	Form B	Form B	Form B	Form B	Form B	Form B	Form B	
Visits to the study center.			X	X	X	X		
Study nurse collects informed consent			Form H					
Study nurse collects baseline data			Form C					
Study nurse collects data				Form D	Form D	Form D		
Acupuncturist registers treatment			Form E	Form E	Form E	Form E		

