### Ethical considerations

Research with children requires careful ethical reflection. Infants in our study are vulnerable and they can not sign the informed consent themselves. Infants with colic suffer and it is important to involve them in research to be able to find effective treatments. In this trial the infants were separated from the parents for five minutes for blinding reasons. Parents were informed about this and could choose not to participate. The separation was done as gently as possible, and when the parent and the infant were ready. For example the mother could breastfeed before leaving the baby to the nurse. The Regional Ethical Review Board in Lund and the Department Manager at each center approved the trial (Dnr 2012/620).

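### Crying caused by needling is to be reported, but the record described is any crying in the treatment room, and no comparison with group C is stated

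*Protocol article*

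**What the plan says.** The Outcome measurement section of the protocol article lists, next to adverse events and parallel treatment, that "how much infants cried from being needled and how well parents are blinded will be reported".

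The data come from the acupuncturist. Interventions says: "The acupuncture nurse treated the baby according to allocation". Without limiting it to the needled arms, the section adds that this nurse "recorded treatment provided, as well as whether the baby cried and, if so, for how long". Data collection describes Form E as holding the points used, "time for stimulation, possible crying and if so for how long". Table 1 lists Form E at all four visits, with no restriction by arm.

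Ethical considerations says that "the infants were separated from the parents for five minutes for blinding reasons", and this applies to the whole trial. For group C, Interventions says: "Infants spent five minutes with the acupuncturist in the treatment room". It adds, for that group only, that the nurse held the infant's hand and spoke calmly. In every arm the stay ends in the same way: "After five minutes, the acupuncturist called the study nurse, who then carried the baby back to the parents".

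The Statistical analysis section compares A and B with C for diary crying. Its list of additional descriptive results covers background data, point choice, centres and blinding. Treatment-room crying is not in that list.

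**The concern.** The item is worded as an effect of the needle, while the record described is an observation in a room. The infants were selected for excessive crying and have just been taken from their parents, so some would probably cry there without any needle.

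A figure for crying due to needling can be taken from such a record in two ways. One is to count all crying in groups A and B, which includes whatever crying would have occurred anyway. The other is to let the acupuncturist judge the cause, and that person gave the treatment and knows the allocation. Neither gives a controlled estimate.

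At stake is what the trial can say about the distress that each type of acupuncture causes. The article's Discussion promises more knowledge about safety in infants, and distress at needling is an obvious part of that.

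**Working it through.** The documents give no rate, standard deviation or target for treatment-room crying, so there is no figure to reproduce. The check sets the stated item against the described measurement.

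**1. Quantity named.** Outcome measurement: crying due to needling. It is causal, and undefined in group C, where no needle is used.

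**2. Quantity recorded.** Interventions and Data collection: crying yes/no, and its duration. Neither section describes the onset of crying relative to insertion, crying on arrival, or a judgement of cause.

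**3. Share of the stay with a needle in place.** The inputs are from Interventions; the stay is about 5 × 60 = 300 s.
- Group A, one needle for 2–5 s: 2/300 = 0.7% to 5/300 = 1.7%.
- Group B, LI4 or ST36, at most 30 s per needle: 30/300 = 10% per needle.
- Group B, Sifeng, four insertions of about one second each: 4/300 = 1.3%.

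Crying from a needle can outlast contact, so these shares do not measure needle crying. They show only that most of the observed time is without a needle in group A, and that a recorded duration can readily include crying with another cause.

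**4. Is there a concurrent reference?** Group C has the same room, the same separation and the same five minutes. The recording sentence covers infants treated according to allocation, and Table 1 shows Form E at every visit. Crying in group C is therefore recorded by implication, although no section names it as the reference.

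**5. What the comparison would give.** Let pA and pC be the proportions of visits with any crying. Counting all crying in group A reports pA. The excess over group C is pA − pC. The two agree only if pC = 0, which cannot be assumed for infants with colic who are separated from their parents. Group B works the same way.

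**6. What the comparison would not give.** Blinding says that the acupuncturist knows the allocation, and this holds in every arm, so the difference does not remove observer bias. Hand-holding and calm speech are described only for group C. The difference therefore estimates the whole needling procedure against soothing without a needle, not the needle alone.

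**The case against.** The strongest reply is that the record itself is neutral and the article is a condensed account. Form E is not shown, and the acupuncturist may note only crying at insertion. The Statistical analysis section says that analyses will use the data from the forms and that A and B are compared with C. How a descriptive item is tabulated is commonly left to a fuller document. Silence about group C is not a decision to leave it out.

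Much of this stands. A reader might infer that the plan credits all treatment-room crying to the needle, or that group C has been set up as the reference and then ignored. The documents support neither: no section says how needle crying is derived from Form E, and none designates group C crying as a reference. A reader might also want a factor for the overstatement. Supposing crying at 50% of needled visits and at 10%, 30% or 40% of group C visits gives 50/40 = 1.25, 50/20 = 2.5 or 50/10 = 5. Those rates have no basis in the documents, and the factors presuppose that all crying is counted.

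What the reply does not remove is the mismatch between the item as worded and the record as described. That is in the text, not an omitted detail. An item defined as crying due to needling leaves no place for group C, so a later table that follows the wording would omit the one group that shows the background level.

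**Conclusion.** The point holds as a minor one. The item is worded as crying caused by needling, the described record does not separate that from other crying, and no comparison with group C is stated for it. The size of any distortion cannot be estimated from the documents.

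The conclusion rests on two assumptions: that Form E holds no more about cause or timing than the article describes, and that it is completed for group C as the text implies. The item is a descriptive measure of tolerability, with no hypothesis or power attached. The primary and secondary diary outcomes are unaffected.

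**What to change.** Redefine the item as any crying in the treatment room, yes/no and duration, per visit in all three arms. Report it by arm, with the A–C and B–C differences and confidence intervals that allow for up to four visits per infant. One summary per infant (the proportion of visits with crying, and mean duration per visit) would be enough, as would a model with infant as the cluster.

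State two limits beside the result: the recorder knew the allocation in every arm, and soothing is described only for group C, so the contrast is the needling procedure against soothing without a needle.

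The cost is one changed sentence and slightly more analysis. It uses data that the article already describes, so it should also cover the infants already included, and no treatment changes. Extra tick boxes on Form E and a censoring rule for crying at hand-back are not needed, since all arms are observed over the same stay of about five minutes.
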